### Informed consent

The acquisition of written informed consent is mandatory for all participants. In cases where participants are unable to provide consent, it must be obtained from their legally designated representatives.

### Sample size calculation

The study conducted by Blackman demonstrated that the 12-week ulcer healing rate in the standard treatment group for diabetic foot ulcers was 42.8%, whereas the wound healing rate in the group receiving TOT was significantly higher at 85.2% [17]. Our previous research documented a wound healing rate of 69% in the standard treatment group for diabetic foot ulcers [22]. Assuming a baseline wound healing rate of 60% in the standard treatment group over a 12-week period, it is hypothesized that the incorporation of TOT would result in a 30% relative improvement in the wound healing rate, i.e., from 60% to 78%. This hypothesis will be evaluated using a two-sided test with a significance level (α) of 0.05 and a statistical power (1-β) of 0.8. Sample size estimation, conducted using PASS 15 software and based on the methodology for comparing two-group proportions in a randomized controlled trial, indicated that each experimental and control group should comprise approximately 100 participants, totaling 250 participants when accounting for an expected dropout rate of approximately 20%.

### Randomization and allocation concealment

The eligible participants will be randomly assigned in a 1:1 ratio to either receive TOT or sham oxygen therapy. Additionally, all subjects will receive standard wound care as prescribed by their attending physician. The random sequence will be generated by a researcher utilizing R software with the simple randomization method. A designated technician will oversee the sequence numbers and monitor the treatment procedures. Both the attending physician and participants will remain blinded to the specific oxygen therapy protocol.

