## Background

Chronic wounds can be attributed to a variety of factors, such as diabetic ulcers, infectious lesions, pressure sores, and traumatic injuries [1]. The management of chronic wounds poses a substantial challenge in contemporary medical practice, owing to their multifactorial etiology, extended treatment duration, significant financial burden, and propensity for recurrence and disability [2]. In high-altitude regions, particular attention has been directed towards addressing refractory chronic wounds within the framework of plateau medicine.

Due to the inherent low-pressure and hypoxic conditions of high-altitude plateaus, combined with persistent tissue hypoxia and decreased perfusion at the wound site, chronic wounds in these regions display distinct pathophysiological characteristics compared to those in plains [3]. A retrospective study conducted at the Qinghai Provincial People’s Hospital indicated that among the elderly residing on the plateau, diabetic foot was the leading cause of chronic wounds, accounting for 51.9% of all cases, followed by pressure sores, post-surgical infections, traumatic ulcers, venous ulcers, and arterial ulcers [4]. The microbial profiles and antibiotic resistance patterns associated with infections in plateau wounds markedly differ from those observed in plains [5]. Chronic wounds in high-altitude settings are especially susceptible to complications such as fat necrosis, incisional infection, wound hematomas, and delayed healing [6]. Furthermore, comorbidities such as chronic cardiopulmonary diseases, which are more prevalent in plateau regions, can exacerbate the challenges associated with non-healing wounds.

However, the recommendations for caring for chronic wounds at high altitudes are not substantially distinct from those in plains. Limited literature has been published to investigate interventions that could enhance wound healing in high-altitude environments. In a study, Zhao et al showed that a plateau refractory chronic wound may heal after platelet lysate gel treatment [7]. Standard of care for chronic wounds includes off-loading, anti-infection strategies, debridement, local wound care, negative-pressure wound therapy, and the application of various dressings. Interventions tailored to address the unique pathophysiology of wounds at high altitudes may offer promising avenues for improving wound healing outcomes.

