#### Inclusion criteria.

① Participants must be aged between 18 and 80 years; ② Participants are required to reside in regions with an elevation of no less than 2,500 meters above sea level; ③ Chronic refractory wounds are defined as those that have not healed within a four-week period, including chronic diabetic skin ulcers and venous insufficiency ulcers of the lower limbs; ④ Adequate blood flow is required, as evidenced by an Ankle-Brachial Index (ABI) of 0.6 or higher, or a transcutaneous oxygen tension exceeding 30 mmHg; ⑤ The ulcer area must measure between 1 and 20 cm^2^.

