### Statistical analysis

R software will be utilized to conduct statistical analyses. The multiple imputation approach will be utilized to address missing data. Statistical analysis will be conducted using an intention-to-treat approach. Specifically, the chi-square test will be utilized to evaluate the primary outcome measure, namely the wound healing rate at 12 weeks. For sparse data, Fisher’s exact test will be used. Logistic regression analysis will be conducted to investigate potential confounding factors that may influence wound healing. Confounding factors, such as sex, age, history of diabetes, ulcer categories, wound area, and infection status, will be adjusted to ensure the reliability of the findings. Subgroup analysis will be conducted according to age, wound categories, and wound area. The reduction rate of ulcer area and wound healing time at 12 weeks were evaluated using either the independent t-test or the Mann-Whitney, contingent upon meeting the assumptions for parametric analysis. Furthermore, the chi-square test will be applied to assess the ulcer recurrence rate and the amputation rate. Kaplan-Meire survival analysis will be performed to compare wound healing between the two groups, with the log-rank test used for statistical comparison. Unadjusted and adjusted Cox proportional hazards models were employed to evaluate the association between TOT therapy and wound healing. Multivariable models were adjusted for covariates such as age, sex, history of diabetes, ulcer categories, wound area, and infection status. A significance level of P < 0.05 will be considered statistically significant.

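### Under simple randomisation the unadjusted primary test makes no use of ulcer category and wound area: valid and unbiased, but less precise than it could be

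*Protocol article*

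**What the plan says.** Under Randomization and allocation concealment, participants are to be "randomly assigned in a 1:1 ratio to either receive TOT or sham oxygen therapy", and "The random sequence will be generated by a researcher utilizing R software with the simple randomization method". No block, stratum or minimisation is mentioned. A technician oversees the sequence numbers and also monitors treatment.

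The Inclusion criteria admit chronic wounds "including chronic diabetic skin ulcers and venous insufficiency ulcers of the lower limbs", with areas from 1 to 20 cm². The Discussion confirms a single centre.

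The Statistical analysis section assigns the primary outcome, healing by 12 weeks, to a chi-square test, or to Fisher's exact test if data are sparse. It also plans logistic and Cox models adjusted for age, sex, diabetes history, ulcer category, wound area and infection, and adds: "Subgroup analysis will be conducted according to age, wound categories, and wound area". The Follow-up section says that assessment of healing will be neither blinded nor centralised.

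**The concern.** The protocol treats ulcer category and wound area as prognostic, since it adjusts for them, and as possible effect modifiers, since it plans subgroups by them. Yet neither the allocation nor the primary test uses them. Any chance difference in ulcer mix between the arms therefore stays in the primary contrast as noise that could have been removed. If the mix turns out uneven, the crude and adjusted results may also differ, and the article does not say which one carries the conclusion. At stake are some power and the ease of interpreting the result, not the validity of the test.

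**Working it through.** **Inputs from the Sample size calculation section.** "a two-sided test with a significance level (α) of 0.05 and a statistical power (1-β) of 0.8"; "a 30% relative improvement in the wound healing rate, i.e., from 60% to 78" per cent; "approximately 100 participants, totaling 250 participants when accounting for an expected dropout rate of approximately 20" per cent.

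**Inputs that are not this trial's own.** The 51.9% share comes from the Background, where in a retrospective series of elderly plateau patients "diabetic foot was the leading cause of chronic wounds, accounting for 51.9% of all cases". It serves only as an illustration. The gap in healing between ulcer categories (20 or 30 points) is an assumption; the document gives none.

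**1. The plan's own figure.** With unpooled variance, n per arm = (1.960 + 0.842)² × (0.60×0.40 + 0.78×0.22) / 0.18² = 7.85 × 0.4116 / 0.0324 ≈ 99.7, so 100. Then 200/0.80 = 250. Both figures reproduce. The pooled-variance formula gives 103 per arm, so the power figures in step 2, which use it, show 79.0% at 100 per arm.

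**2. Arm sizes.** One arm is Binomial(N, 0.5).
- N = 250: SD √250/2 = 7.9, 95% range 110 to 140. The chance that the arms differ by 20 or more is 0.23, and by 30 or more 0.066.
- Power with equal arms is 87.3% at N = 250 and 79.0% at N = 200. Averaged over simple randomisation it is 87.1% and 78.8%, a loss of 0.1 to 0.2 points.
- At the worse 95% extreme for N = 200 (114:86) power is 77.9%, about 1.2 points below equal arms.

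**3. Ulcer mix.** The SD of the between-arm difference in a category with share q is √(4q(1−q)/N). With q = 0.519:

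| N | SD (points) | 95% range (points) | Chance of more than 10 points |
|---|---|---|---|
| 250 | 6.3 | ±12.4 | 0.11 |
| 200 | 7.1 | ±13.8 | 0.16 |

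For a category with a 20% share the chance is 0.05 at N = 250 and 0.08 at N = 200.

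**4. Effect on the primary contrast.** Multiply by the assumed gap. At N = 250 the component due to mix has SD 6.3 × 0.20 to 0.30 = 1.3 to 1.9 points. The standard error of the crude difference at 125 per arm is √(0.4116/125) = 5.7 points. Mix therefore supplies about (1.3/5.7)² to (1.9/5.7)², or 5% to 11%, of the variance. At the 95% extreme the shift is 2.5 to 3.7 points at N = 250, and 2.8 to 4.2 points at N = 200, against a planned effect of 18.

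**5. Simulation.** N = 200, 40,000 runs per cell, two categories (51.9% and 48.1%), mean control healing 60%, effect 18 points in both. Stratified allocation splits each category evenly, which idealises permuted blocks. Adjusted means Mantel-Haenszel by category. Monte Carlo error of a power figure is about √(0.8×0.2/40,000) = 0.2 points.

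| Allocation, test | Type I error, 20-point gap | Power, 20-point gap | Type I error, 30-point gap | Power, 30-point gap |
|---|---|---|---|---|
| Simple, unadjusted (as planned) | 4.9% | 79.4% | 5.2% | 79.3% |
| Simple, adjusted | 5.0% | 81.0% | 5.2% | 83.2% |
| Stratified, unadjusted | 4.5% | 80.4% | 4.0% | 81.0% |
| Stratified, adjusted | 5.0% | 81.1% | 4.9% | 84.3% |

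Adjustment brings most of the gain. Stratification on top of it adds about 1 point at the 30-point gap and nothing measurable at the 20-point gap. Stratifying while keeping the crude test makes that test conservative.

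**6. Subgroups.** In a category of 40 patients a split of 60:40 or worse has probability 0.27. With similar variance in both arms, a 60:40 split still keeps 4 × 0.6 × 0.4 = 0.96 of the efficiency of an even one.

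**The case against.** The strongest reply is that nothing here is an error. Allocation with probability one half is a 1:1 ratio, the crude test holds its level (4.9% to 5.2% in simulation), and its standard error already includes chance imbalance. The protocol also plans models adjusted for the very factors in question. All of this stands, and it rules out several stronger readings:

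- A reader might infer that simple randomisation contradicts the stated ratio or biases the result. It does neither: the ratio holds in expectation, and an uneven mix is random error, not bias.
- A reader might take the 110 to 140 range as a serious threat to power in a small trial. With 250 participants the average cost is 0.1 to 0.2 points.
- A reader might infer that the protocol ignores prognostic factors. It does not; it adjusts for them, but outside the test assigned to the primary outcome.
- A reader might call stratified blocks free. They are not. Blocks within strata at one centre are easier to guess than simple randomisation. The attending physician is blinded, but outcome assessment is not, and researchers screen, treat and follow up the participants. Simple randomisation is the least predictable scheme.

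What the reply does not remove is that the primary contrast makes no use of baseline information that the protocol already plans to analyse.

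**Conclusion.** The point holds as a minor matter of efficiency, and it concerns the primary analysis more than the randomisation. The planned combination is valid, but it gives up about 1.6 points of power at an assumed 20-point gap between categories (79.4% v 81.0%) and about 4 points at 30 (79.3% v 83.2%), with 200 participants. If ulcer category predicts healing only weakly, the gain shrinks towards nothing. The chance of a visible imbalance, above 10 points in a category of about half the participants, is 11% to 16%. These sizes rest on a borrowed category share and an assumed gap. The simulation adjusts for category only, so any gain from adjusting for area is not counted.

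**What to change.** 1. Make the primary analysis a pre-specified comparison adjusted for ulcer category and baseline area: for example, logistic regression reported as a standardised risk difference, or Mantel-Haenszel with area in bands. Keep the crude chi-square as supportive, and state that the adjusted result carries the conclusion. Both factors are already in the planned models, so the cost is a short amendment, made before any outcome is examined by arm.

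2. For remaining participants, generate the sequence in R as concealed permuted blocks of random size, stratified by ulcer category. Keep the list from anyone who screens, enrols or assesses outcomes, and record the date of the change. The cost is a few lines of code and somewhat greater predictability, which random block sizes and concealment limit. Do this only together with step 1, because stratified allocation makes the crude test conservative.

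If enrolment is too far advanced for step 2, step 1 alone secures most of the benefit.

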### Interventions

Following randomization, all participants will be assigned to either the treatment group, which will receive TOT, or the control group, which will undergo sham therapy. Additionally, all patients will receive standard medical care for chronic wounds, which include the management of blood sugar, blood pressure, and lipid profiles; antiplatelet aggregation and anticoagulation therapies; infection prevention measures; promotion of physical activity; pressure relief interventions; and debridement procedures. The application of platelet-rich gel and negative pressure wound therapy will also be incorporated. To ensure that all patients received standard wound care, a checklist with the abovementioned contents will be used in the study.

Treatment Group: In addition to receiving standard care for chronic wounds, patients will undergo TOT at their bedside within the ward. This therapy will be delivered using the lower limb wound oxygen therapy device (G00001) supplied by Odie Oxygen Therapy Company, based in Ireland. The treatment involves the delivery of pressurized oxygen, with a pressure range of 0–50 mbar, generated by an oxygen concentrator operating at a flow rate of 10 L/min. Each session will last 90 minutes and will be conducted once daily, five days per week.

Control Group: Patients in the control group received standard wound care and sham therapy. The sham devices looked and operated identically with the active TOT therapy, with the sole difference being the use of ambient air as the gas source instead of an oxygen supply.

### Outcomes

#### Primary outcomes.

The wound healing rate at 12 weeks: the proportion of participants achieving complete wound healing, defined as full epithelialization of the wound within a 12-week timeframe.

#### Secondary outcome.

Rate of ulcer area reduction: percent change in wound size after 12 weeks of treatmentTime to ulcer healing: duration until complete wound closureOne-year ulcer recurrence rate: proportion of ulcers that recur within one-year post-healingAmputation rate at 12 weeks: incidence of amputation within the first 12 weeksVAS score: Visual analogue scale for pain assessmentWound-QoL: Questionnaire assessing quality of life in patients with chronic wounds

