**Methods and analysis:**

This study is a randomized controlled clinical trial involving 250 patients residing at high altitudes. Participants will be randomly assigned to receive either TOT or sham oxygen therapy over a 12-week period, followed by a one-year follow-up. In addition to the experimental interventions, all participants will receive standard care for their chronic wounds. The primary outcome measure is the wound healing rate at the end of the 12-week intervention. Secondary endpoints include the reduction in ulcer area after intervention, the time required for ulcer healing, the recurrence rate of ulcers, the amputation rate, pain levels, and any adverse events.

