### Study population

The recruitment of patients with chronic refractory wounds from high-altitude regions will be conducted at West China Hospital, Sichuan University. All individuals seeking treatment for chronic wounds in high-altitude areas will undergo a comprehensive and rigorous screening process based on predefined inclusion and exclusion criteria. Following the acquisition of informed consent, eligible patients with chronic refractory wounds from these regions will be enrolled in the study. This trial is scheduled to commence in Oct. 2024 and is expected to conclude by June 2026.

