### Follow-up

Patients will be randomly allocated to either the treatment group or the control group and will receive the respective interventions until complete wound healing occurs or for a maximum duration of 12 weeks. Digital photography will be employed to systematically document images on a weekly basis. The researchers will determine whether the outcomes were reached. Because of the objective feature, the outcome assessment for wound healing will not be blinded or centralized. The Image J software will be utilized to quantitatively measure the area of the foot ulcer during each debridement and dressing change procedure. The total follow-up period will span one year, with evaluations conducted at 4-, 8-, 12-, 24-, and 52-weeks post-randomization to assess wound healing, ulcer recurrence, and the incidence of amputation. The items to be measured and the time window of data collection are shown in Fig 1.

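### Recurrence is defined over one year from healing, but the scheduled visits end 52 weeks from randomisation, and the planned chi-square test ignores both the shortfall and the selection of healed ulcers

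*Protocol article*

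**What the plan says.** The protocol article gives three time frames that do not fit together.

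- **Secondary outcome:** one-year recurrence is the "proportion of ulcers that recur within one-year", with the year counted from healing.
- **Follow-up:** "The total follow-up period will span one year, with evaluations conducted at 4-, 8-, 12-, 24-, and 52-weeks post-randomization". These visits assess healing, recurrence and amputation. Treatment runs "until complete wound healing occurs or for a maximum duration of 12 weeks".
- **Abstract, Methods and analysis:** participants are treated "over a 12-week period, followed by a one-year follow-up", which reads as about 64 weeks from randomisation.

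Under Statistical analysis, "the chi-square test will be applied to assess the ulcer recurrence rate and the amputation rate". Kaplan-Meier, log-rank and Cox methods are named for wound healing only, and no censoring rule is given for recurrence. The same section states an intention-to-treat approach in general terms. The trial is "scheduled to commence in Oct. 2024 and is expected to conclude by June 2026" (Study population).

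**The concern.** The endpoint's clock starts at healing and the visit clock starts at randomisation. Unless a wound heals on the day of randomisation, a schedule that stops at week 52 cannot give it a full year after healing. The trial would then report a one-year recurrence rate that it had not measured.

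Two further questions follow for the comparison between arms. First, a chi-square test treats 40 and 48 weeks of observation as the same, so an arm that heals faster has longer to show recurrences. Second, only a healed ulcer can recur, and the trial is designed in the expectation that the healed fractions differ. The healed groups are then formed by an outcome of treatment rather than by randomisation.

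**Working it through.** **Inputs from the protocol.** Last visit at week 52 and treatment for at most 12 weeks (Follow-up). Healing by week 12 of 60% on control and 78% on TOT (Sample size calculation). The documents give no recurrence rate, so every recurrence rate below is an assumption, shown over a range.

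**The plan's own figure.** There is no sample size for recurrence. The primary calculation, which supplies 60% and 78%, reproduces: (1.960 + 0.842)² × (0.60×0.40 + 0.78×0.22) / 0.18² = 99.7, so 100 per arm, and 200/0.80 = 250. (Pooled variance gives 103 per arm.)

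**1. Observable time after healing.** Weeks observed = 52 − week of healing. At constant hazard with true one-year recurrence R, the observed proportion is 1 − (1 − R)^(weeks/52).

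| Healed at week | Weeks observed | Share of the year | R = 20% | R = 30% | R = 40% |
|---|---|---|---|---|---|
| 4 | 48 | 92% | 18.6% | 28.1% | 37.6% |
| 8 | 44 | 85% | 17.2% | 26.1% | 35.1% |
| 12 | 40 | 77% | 15.8% | 24.0% | 32.5% |

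On the abstract's reading, 64 − 12 = 52 weeks, so every ulcer healed by week 12 would have its full year.

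**2. Does unequal observation bias the comparison?** Assume exponential healing with rate λ = −ln(1 − p)/12, that is 0.0764 per week on control and 0.1262 on TOT. Mean healing time among ulcers healed by week T is 1/λ − T·exp(−λT)/(1 − exp(−λT)).

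- T = 12: 13.10 − 8.00 = 5.10 weeks on control and 7.93 − 3.38 = 4.54 on TOT. Mean observation is 46.9 v 47.5 weeks, a gap of 0.6. At R = 30%, observed recurrence is 27.5% v 27.8%. With 60 v 78 healed per 100 randomised, the chi-square type I error is about 0.050 for R from 20% to 40%.
- T = 52: mean observation is 39.9 v 44.1 weeks, a gap of 4.2. At R = 30%, observed recurrence is 23.7% v 26.0%. Type I error is 0.060 at R = 20%, 0.066 at 30% and about 0.072 at 40%. This case carries the exponential curve to week 52, by which time nearly every ulcer has healed (98% v more than 99%), so it is a generous allowance for late healing.

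**3. Selection on healing.** Suppose 60% would heal in either arm and recur at 30%, a further 18% heal only on TOT and recur at rate r, and TOT has no effect on recurrence. TOT recurrence among healed = (0.60×0.30 + 0.18×r)/0.78. Healed and ulcer-free among all randomised = 0.60×0.70 + 0.18×(1 − r) on TOT, and 0.60×0.70 = 42% on control.

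| r | Recurrence among healed, TOT v control | Healed and ulcer-free, TOT v control | Type I error, 78 v 60 healed |
|---|---|---|---|
| 30% | 30.0% v 30% | 54.6% v 42% | 0.05 |
| 45% | 33.5% v 30% | 51.9% v 42% | 0.07 |
| 60% | 36.9% v 30% | 49.2% v 42% | 0.13 |

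**The case against.** The strongest reply is that the mismatch is one of wording. The abstract can be read as 64 weeks, which agrees with the outcome definition for every ulcer healed by week 12. Only the Follow-up section is then out of line, and the schedule figure is not available to settle the matter. This stands as far as it goes: the protocol does not show that one-year recurrence is unobservable outright, although a reader might infer that. Even on the 52-week schedule, a week-12 healer is seen for 40 weeks and recurrences in that time can be counted. But no visit after week 52 is described, so someone running the trial from the text cannot deliver the defined year.

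A reader might also infer a sizeable exposure bias from the healing times in the Background, 56 v 93 days. These leave 364 − 56 = 308 v 364 − 93 = 271 days, about 14% more on TOT. The documents do not support carrying that over. The figures come from another study, and 93 days lies beyond the 84-day treatment window. If 93 days is a median, it also conflicts with this protocol's 60% control healing by week 12, which puts the median at or before day 84. On the trial's own rates the gap is 0.6 weeks.

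The healed-only denominator is not written out. It is the natural reading of a rate counted after healing, so a departure from intention-to-treat is inferred, not stated. Taking all randomised as the denominator would not help: with 30% recurrence after healing in both arms, TOT shows 0.78×0.30 = 23.4% against 0.60×0.30 = 18.0%, simply because more wounds healed. That the outcome counts ulcers rather than participants is a thin complaint, since nothing in the text describes several study ulcers per participant.

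**Conclusion.** The inconsistency is certain: the outcome definition, the Follow-up section and the abstract cannot all hold. On the visit schedule no healed ulcer receives the defined year. A week-12 healer gets 77% of it, and an assumed 30% rate appears as about 24% at constant hazard.

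The chi-square test is poorly matched to this variable follow-up, but the harm to the comparison between arms should not be overstated. It is negligible if only healing by week 12 counts. It is modest, with a gap of about 4 weeks and type I error of 0.06 to 0.07, if later healing counts, which the healing assessments at weeks 24 and 52 leave open.

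Selection on healing is the larger risk for interpretation. Its size depends wholly on an assumption about the extra healers: none if they recur like the others, and 36.9% v 30% if they recur at 60%. It would go too far to say that TOT will look worse on recurrence. The supported statement is that a comparison among healed ulcers is not randomised and could mislead in that direction.

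Recurrence is a secondary outcome, so the primary analysis is untouched.

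**What to change.** 1. **Settle one follow-up length** across the abstract, the outcome definition and the Follow-up section, by one of two routes.
   - Define the endpoint as recurrence by week 52 after randomisation. This needs no new visit but gives up the label of one year post-healing.
   - Keep the year from healing and schedule follow-up to 52 weeks after closure, up to week 64 for ulcers healed by week 12. From October 2024 to June 2026 is about 20 months. Twelve further weeks take nearly 3 months from recruitment unless the end date moves, and the Discussion already expects recruitment to be difficult.
2. **Replace the chi-square test for recurrence** with Kaplan-Meier time from healing to recurrence, censored at the last visit. The plan already uses this method for healing. State whether healing after week 12 enters the analysis. On the 52-week schedule, quote the estimate at 40 weeks after healing, which every completer healed by week 12 can reach.
3. **Label the healed-only comparison as non-randomised** and descriptive.
4. **Add a supportive analysis of all randomised participants:** the proportion healed by week 12 and ulcer-free at week 52. The scheduled visits already collect the data.

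With the week-52 definition, the cost is a protocol amendment in a registered, ethics-approved trial, with the registry entry checked to match, and no extra data collection. The second route adds visits and a later end date or a shorter recruitment period.
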